### Participants

2.2

Participants aged 60 years or older will be recruited, consistent with internationally recognized SCD-Initiative consensus criteria proposed by Jessen et al. (2014). Eligible individuals must report a subjective perception of cognitive decline persisting for more than 6 months and not attributable to a specific acute event, in accordance with criteria described by Molinuevo et al. (2017). SCD will be formally confirmed based on the SCD-Initiative criteria (Jessen et al., 2014), incorporating both self-report and a structured clinical interview. All participants must provide written informed consent and meet the inclusion and exclusion criteria detailed below.

Increasing evidence suggests that therapeutic interventions targeting earlier stages of neurodegenerative disease may yield greater clinical benefit compared with interventions initiated at more advanced stages. For example, disease-modifying therapies such as donanemab have been investigated primarily in individuals with early symptomatic Alzheimer’s disease (MMSE score of 20–28), reflecting the growing emphasis on early intervention (Mintun et al., 2021). Similarly, cognitive training strategies are recommended when implemented at earlier phases of cognitive decline (He et al., 2023). Based on this evidence, we selected individuals with SCD, who represent a preclinical or very early stage along the cognitive decline continuum, rather than patients with MCI. This approach allows evaluation of whether structured cognitive training may exert measurable effects prior to substantial neurodegeneration, thereby maximizing the potential sensitivity for detecting both behavioral and biological changes.

As part of the screening process, we will administer the “Abbreviated Memory Inventory for the Chinese” developed by Chinese University of Hong Kong (Lam et al., 2005). The instrument consists of five questions assessing subjective memory concerns.

Forgetting where things are placed?Unable to recall the names of good friends?Unable to follow and recall conversation?Subjective memory problems?Consider own memory to be worse than others of a similar age?

Prior evidence indicates that an increasing frequency of subjective memory complaints is associated with higher Clinical Dementia Rating (CDR) scores. Specifically, individuals endorsing more than three out of five items on the Abbreviated Memory Inventory for the Chinese are more likely to be associated with MCI or Alzheimer’s disease. Notably, previous findings also demonstrated that subjective memory complaints are highly prevalent among cognitively normal individuals, with approximately 70.2% reporting subjective memory problems and 63.8% reporting difficulty recalling the location of objects (Lam et al., 2005). These observations are consistent with our clinical experience and highlight the need to distinguish early-stage SCD from more advanced cognitive impairment.

To balance sensitivity for detecting SCD while minimizing the inclusion of participants with undiagnosed MCI, we adopted a threshold of “at least two” positive responses on the five-item inventory as an eligibility criterion. This cutoff allows inclusion of individuals with meaningful subjective cognitive concerns while reducing the likelihood of enrolling participants with more advanced cognitive impairment. To exclude early MCI, all participants will undergo objective cognitive assessment using standardized instruments (e.g., MoCA score ≥26) (Sun R. et al., 2023). Individuals performing 1.5 SD or more below age- and education-adjusted norms on any cognitive domain will be excluded. Given that depressive and anxiety symptoms can independently contribute to subjective cognitive complaints, all participants will be screened using the Geriatric Depression Scale (GDS) and/or the Generalized Anxiety Disorder scale (GAD-7). Individuals meeting clinical thresholds for significant depression or anxiety will be excluded, or alternatively, these scores will be included as covariates in the statistical analysis.

Exclusion criteria:

Objective cognitive impairment defined as ≥1.5 standard deviations below standardized cognitive testing (e.g., MMSE) (Belleville et al., 2023).Diagnosis of MCI (e.g., MoCA score <26) (Sun R. et al., 2023).Clinical Dementia Rating (CDR) ≥ 0.5 (Molinuevo et al., 2017).Diagnosis of major depressive disorder (Molinuevo et al., 2017).Beck Anxiety Inventory score ≥16 (means moderate to severe anxiety).Other medical or neurological conditions that could explain cognitive decline (e.g., vascular dementia, traumatic brain injury).Claustrophobia.Contraindications of MRI (e.g., non-MRI-compatible cardiac pacemaker or devices implanted within the past 3 months).

### Sample size

2.3

Our sample size calculation is based on selecting functional MRI changes as an exploratory mechanistic outcome measure, given their higher sensitivity than neuropsychological tests at the preclinical stage in SCD patients (Viviano and Damoiseaux, 2020). This approach differs from many previous cognitive intervention studies that have used neuropsychological test scores as primary outcomes. The target sample size is informed by prior neuroimaging studies in individuals with SCD, where changes in functional MRI parameters served as the primary outcomes (Bhome et al., 2018), while also considering feasibility constraints (Belleville et al., 2023). Accordingly, we plan to recruit 60 participants, with 30 individuals allocated to each group. To account for an anticipated attrition rate of approximately 20%, based on dropout rates reported in comparable longitudinal cognitive intervention studies in older adults (Cheng et al., 2024; Fernandez-Gamez et al., 2026), we will initially enroll 72 participants (36 per group), with the expectation that at least 60 will complete the study.

If neuropsychological test scores were used as the primary outcome, a substantially larger sample size would be required. An *a priori* power analysis was conducted using G*Power version 3.1.9.4 (Heinrich Heine University, Düsseldorf, Germany), based on a two-group comparison of continuous outcomes within the t-test family (“Means: Difference between two independent means”). Equal group allocation was assumed (N₂/N₁ = 1), and a one-tailed test was selected given the directional hypothesis that the intervention would improve outcomes. The anticipated standardized effect size was set at Cohen’s d = 0.18, derived from prior meta-analytic evidence indicating a small-to-moderate effect consistent with neuroimaging-based outcomes in SCD populations (Bhome et al., 2018). With a Type I error rate (*α*) of 0.05 and statistical power (1 − *β*) of 0.80, the estimated required sample size would be 383 participants per group (total *N* = 766; df = 764; actual power = 0.8006). Given the extensive multimodal assessments and longitudinal design of the present study, recruiting a sample of this magnitude is not feasible. Therefore, this study is designed as an exploratory, hypothesis-generating trial with a smaller sample size, aiming to provide preliminary effect estimates and inform future large-scale confirmatory studies.

The present study acknowledges that the planned sample of 60 participants is underpowered for the neuropsychological and other multimodal secondary outcomes. The adequacy of statistical power for these secondary outcomes — which include cognitive test scores, subjective cognitive measures, and additional neuroimaging parameters — was not the basis for the sample size determination and should be interpreted with caution. Effect sizes from secondary outcomes in this pilot trial will inform power calculations for future definitive trials.

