**Methods:**

A total of 60 individuals with subjective cognitive decline will be enrolled in a randomized, assessor-blinded, controlled pilot study. Participants will be randomly assigned to either an intervention group or a non-active control group prior to baseline assessment. The intervention group will undergo a six-month structured recitation training program. Both groups will undergo short-term follow-up after the intervention, and long-term follow-up annually post-intervention. Multimodal assessments will include neuropsychological testing, functional magnetic resonance imaging (fMRI), electroencephalography (EEG), blood biomarker profiling, gut microbiota analysis, and fecal metabolomics.

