### Theoretical framework and mechanistic rationale

3.1

Among non-pharmacological cognitive interventions for SCD, computerized cognitive training (CCT) — the most extensively studied approach — yields a small but statistically significant overall effect on untrained cognitive outcomes in healthy older adults (Hedges’ *g* = 0.18, 95% CI 0.14 to 0.23), with benefits primarily in processing speed, working memory, and non-verbal memory, though with considerable heterogeneity across trials (*I*^2^ = 58%) and wide prediction intervals spanning negligible to moderate effects (−0.36 to 0.73) (Lampit et al., 2020). Exercise-based interventions represent a second major modality; a network meta-analysis of exercise interventions specifically in SCD populations found that, while exercise improved multiple cognitive domains, it remained unclear which type of exercise was most effective, and no single modality demonstrated consistent superiority (Chen et al., 2024). Combined cognitive-physical interventions produce a small advantage over single-domain cognitive training on executive functions, but achieve similar effects on memory and global cognition (Rieker et al., 2022). Notably, a network meta-analysis of pharmacological and non-pharmacological interventions for SCD across 56 randomized controlled trials found that education-based programs ranked highest for improving both memory and global cognition — above CCT, physical exercise, and pharmacological approaches — suggesting that structured, content-rich verbal-cognitive engagement may be a particularly promising avenue (Roheger et al., 2021).

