Despite growing evidence for the general benefit of cognitive interventions in aging, the magnitude and consistency of effects vary substantially across trials, limiting the conclusions that can be drawn from aggregate findings. A comprehensive systematic review of interventions specifically targeting SCD found that, while cognitive training yielded a small statistically significant improvement in objective performance overall (*g* = 0.13, 95% CI 0.01 to 0.25), effect sizes became non-significant when studies used active control groups (*g* = 0.02) or reported global cognitive outcomes (*g* = 0.06), indicating that published effects may largely reflect expectancy and practice artifacts rather than genuine cognitive benefit (Roheger et al., 2021). Heterogeneity of effects is attributable to multiple sources, including variability in SCD diagnostic criteria, differences in intervention dosage and delivery format, inconsistent outcome measurement across domains, and the absence of standardized follow-up periods. In addition, the methodological quality of published cognitive intervention trials in SCD and related preclinical populations remains a significant concern. The majority of trials suffer from one or more of the following limitations: inadequate sample sizes, short intervention durations with no long-term follow-up, outcomes measured only on trained tasks rather than ecologically valid measures, high or unclear risk of bias due to lack of assessor blinding, and failure to conduct intention-to-treat analyses (Roheger et al., 2021). Beyond sample size and reporting concerns, cognitive intervention trials face several systematic biases that may inflate apparent treatment effects. The most pervasive is performance bias from expectancy effects, in which participants believe they are receiving an active intervention and therefore may perform better on outcome assessments regardless of the intervention’s true efficacy. A systematic review of computerized cognitive training trials in healthy older adults found that only 47% included an active control condition, and only 21% measured participants’ expectations — meaning that the majority of published positive findings cannot rule out expectancy as a major contributor to the observed effects (Masurovsky, 2020). To address the gap limited by short follow-up periods, inadequate control of participant expectancy effects, and a predominant reliance on behavioral outcomes without accompanying biological measures in previous studies, this pilot study will incorporate long-term annual follow-ups, administer the credibility and expectancy questionnaire to monitor and statistically adjust for expectancy at baseline and post-intervention, and employ a multimodal assessment framework integrating cognitive, neuroimaging, metabolomic, and gut microbiota measures.

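### At the stated 20% attrition, enrolling 72 leaves about 58 completers, not at least 60, and the Abstract gives the enrolment as 60

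*Protocol article*

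**What the plan says.** The Methods paragraph of the Abstract states: "A total of 60 individuals with subjective cognitive decline will be enrolled in a randomized, assessor-blinded, controlled pilot study".

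Section 2.3 first states "we plan to recruit 60 participants, with 30 individuals allocated to each group". It then introduces the dropout allowance, "To account for an anticipated attrition rate of approximately 20" per cent, and concludes "we will initially enroll 72 participants (36 per group), with the expectation that at least 60 will complete the study". The closing paragraph of section 2.3 again calls 60 the planned sample.

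Section 2.3 also gives a hypothetical calculation for the case where neuropsychological scores were the primary outcome: d = 0.18, one-sided alpha 0.05, power 0.80, 383 per group. It describes that effect as a "small-to-moderate effect consistent with neuroimaging-based outcomes in SCD populations" and rejects the resulting size as not feasible. Section 3.1 reports two related figures from other reviews. Computerised training "yields a small but statistically significant overall effect on untrained cognitive outcomes in healthy older adults", with g = 0.18 (95% CI 0.14 to 0.23). In SCD, "cognitive training yielded a small statistically significant improvement in objective performance overall", with g = 0.13 (95% CI 0.01 to 0.25).

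**The concern.** The enrolment target, the attrition rate and the expected number of completers are linked by one line of arithmetic, and the three stated values do not fit together. 72 is exactly 60 increased by 20%. That is the familiar slip of multiplying by one plus the dropout rate instead of dividing by one minus it.

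Separately, a reader of the Abstract would take 60 as the number randomised, while section 2.3 makes it 72 and uses 60 both for the number to be recruited and for the number who finish. At stake is the trial's headline size. It is what recruitment and retention will be judged against, and both matter in a pilot whose stated aims include feasibility.

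The description of d = 0.18 is a lesser matter. Section 2.3 applies the value to neuropsychological scores but characterises it by reference to neuroimaging outcomes in SCD. The only other 0.18 in the document belongs to healthy older adults.

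**Working it through.** **Inputs.** All are from section 2.3 unless noted: target 60 (30 per arm); attrition about 20%; enrolled 72 (36 per arm); expected completers at least 60. Enrolled according to the Abstract: 60.

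**1. Reproducing the 72.**
- 60 × (1 + 0.20) = 72, and 30 × 1.20 = 36 per arm. This reproduces the stated figures.
- Dividing by retention: 60 / (1 − 0.20) = 75. By arm, 30 / 0.80 = 37.5, so 38 per arm and 76 in total.

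**2. What 72 delivers.**
- Expected completers: 72 × 0.80 = 57.6; per arm 36 × 0.80 = 28.8.
- Shortfall against 60: 60 − 57.6 = 2.4 participants.
- Largest attrition at which 60 are expected to remain: 1 − 60/72 = 16.7%.

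**3. Sensitivity to the word approximately.** The last column is the exact binomial probability that 60 or more of 72 complete, assuming participants drop out independently with a common probability.

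| True attrition | Expected completers | P(60 or more) |
|---|---|---|
| 15% | 61.2 | 0.72 |
| 16.7% | 60.0 | 0.58 |
| 18% | 59.0 | 0.46 |
| 20% | 57.6 | 0.30 |
| 22% | 56.2 | 0.17 |
| 25% | 54.0 | 0.06 |

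**4. Enrolment numbers side by side.** Abstract: 60 enrolled. Section 2.3, first paragraph: 60 to be recruited, then 72 enrolled with at least 60 completing. Section 2.3, last paragraph: planned sample of 60. The only reading that joins these is that 60 means completers, but the Abstract says enrolled.

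**5. The hypothetical calculation.** For a two-sample t-test (noncentral t, one-sided alpha 0.05, d = 0.18), power is 0.7997 at 382 per group and 0.8006 at 383. The stated 383 per group and actual power of 0.8006 therefore reproduce exactly. With g = 0.13 the same method gives 733 per group. Neither number enters the derivation of 60 or 72.

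**The case against.** The best defence is that attrition is stated only as approximate, that 16.7% would make 72 correct, and that little depends on the exact count. The gap is 2.4 participants. No power claim rests on 60 completers. Section 2.5.2.5 analyses all randomised participants with mixed models and multiple imputation, so completers do not define the analysis set. All of this stands as a limit on the consequence. It does not rescue the figures: at least 60 is worded as a floor, 72 is exactly the multiplied figure, and at the protocol's own 20% the floor is missed more often than it is met. Nor does it explain the different enrolment number in the Abstract.

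Four stronger readings are tempting, and the document does not support them.

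- **The power calculation is wrong.** It is not. 383 per group is correct for d = 0.18, and it is a hypothetical that the section itself rejects.
- **d = 0.18 contradicts the document's SCD figure.** Section 2.3 attributes 0.18 to a different review from the one behind 0.13, and 0.18 lies inside that review's interval of 0.01 to 0.25. Whether the source cited in section 2.3 reports 0.18 cannot be checked here. A smaller effect would only strengthen the statement that such a trial is infeasible.
- **The fMRI outcome is shown to be underpowered at 0.18.** That depends on reading one ambiguous phrase as applying 0.18 to imaging. Section 2.3 introduces the value for neuropsychological scores and calls the whole trial exploratory, and section 3.2 says without restriction to secondary outcomes that power may be limited.
- **The pilot's effect sizes cannot serve a later trial with an active control.** The plan does say "Effect sizes from secondary outcomes in this pilot trial will inform power calculations for future definitive trials", but sections 2.1 and 3.2 disclose the missing active control and recommend one for definitive trials. Replacing a stated aim on that ground is a separate methodological preference, not an error in these figures.

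**Conclusion.** Two corrections are warranted. First, 72 enrolled at 20% attrition leaves about 57 to 58 completers (about 29 per arm), not at least 60. The chance of reaching 60 is about 30% at a true 20%, assuming independent dropout with a common rate. Second, the Abstract and section 2.3 disagree on the number enrolled, 60 against 72. Both follow from the document's own numbers and need no outside source.

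The description of d = 0.18 is a request for clarification, not a demonstrated error. The practical effect of the whole point is modest: the stated completer count and the headline enrolment are unreliable as written, but no analysis or power statement falls with them.

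**What to change.** - **Section 2.3:** keep 72 enrolled (36 per arm) and state that about 57 to 58 are expected to complete at 20% attrition, and 60 only if attrition is 16.7% or less. If an expected 60 completers is wanted at 20%, enrolment must be 75, or 76 for equal arms.
- **Abstract and both mentions of 60 in section 2.3:** say each time whether the number is enrolled or completing, and give 72 as enrolled.
- **Description of d = 0.18 in section 2.3:** state the source, population and outcome type that the value refers to, and reconcile the neuroimaging phrase with its use for neuropsychological scores and with the 0.18 and 0.13 in section 3.1. The 383 per group can stay as long as d = 0.18 stays.

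If 72 is kept, the cost is wording only and the completer figure becomes slightly less favourable. Moving to 75 or 76 would add three or four participants, each with the full multimodal assessment.

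### Section 2.3 inflates 60 by 1.2 instead of dividing by 0.8, so 72 enrolled gives about 57–58 expected completers at 20% attrition, not at least 60; the abstract also enrols 60, not 72

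*Protocol article*

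**What the plan says.** Section 2.3 of the protocol article first sets the target: "we plan to recruit 60 participants, with 30 individuals allocated to each group". The next sentence begins "To account for an anticipated attrition rate of approximately 20" per cent, refers to dropout in comparable longitudinal studies, and concludes: "we will initially enroll 72 participants (36 per group), with the expectation that at least 60 will complete the study". The last paragraph of the section, a caveat about power, says that "the planned sample of 60 participants is underpowered for the neuropsychological and other multimodal secondary outcomes".

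The Methods part of the abstract gives one number only: "A total of 60 individuals with subjective cognitive decline will be enrolled". It does not mention 72.

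**The concern.** A single sentence in section 2.3 gives the attrition rate, the number enrolled and the number expected to complete, and the third does not follow from the first two. The number 72 is what results from adding 20% to 60. That is a common slip, because the loss applies to those enrolled and not to those who complete.

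Separately, the documents use enrolment wording for two different totals. The abstract attaches it to 60. Section 2.3 attaches recruitment to 60 and enrolment to 72, and nowhere explains that 60 is meant as a completer count.

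At stake is a clear statement of how many people the trial will randomise and how many it should expect to retain. Feasibility is a stated primary aim (end of the Introduction) and the trial is meant to inform the size of later trials (section 2.1), so these figures should be right and should be the same throughout.

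**Working it through.** **Inputs, all from the protocol article**

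- Target: 60 in total, 30 per group (section 2.3).
- Attrition: about 20% (section 2.3).
- Enrolment: 72 in total, 36 per group; completers expected: at least 60 (section 2.3).
- Enrolment in the abstract: 60.

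**Reproducing the stated 72**

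- Multiplying by one plus the loss: 60 × (1 + 0.20) = 72. This is the plan's figure.
- Dividing by the retained fraction: 60 / (1 − 0.20) = 75. Per arm, 30 / 0.80 = 37.5, rounded up to 38, or 76 in total.

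The plan's 72 is reproduced only by the multiplication, which does not correct for a loss taken from those enrolled.

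**Forward check from 72**

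- Expected completers at 20%: 72 × 0.80 = 57.6 (28.8 per arm), which is 60 − 57.6 = 2.4 short, or 4.0% of 60.
- Attrition at which 60 of 72 remain: 12 / 72 = 16.7%.
- Probability of at least 60 completers, taking each participant as retained independently with probability 0.80: P(X ≥ 60), X ~ Binomial(72, 0.80), = 0.295.

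**Range, because the rate is approximate**

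| Attrition | Expected completers of 72 | P(at least 60) |
|---|---|---|
| 15% | 61.2 | 0.72 |
| 16.7% | 60.0 | 0.58 |
| 18% | 59.0 | 0.46 |
| 20% | 57.6 | 0.30 |
| 25% | 54.0 | 0.06 |

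**Effect on precision, as a completer-only approximation**

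The 95% half-width for a standardised difference is about 1.96 × √(2/n), with n per arm.

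- n = 30: 1.96 × √(2/30) = 0.506.
- n = 28.8: 1.96 × √(2/28.8) = 0.517.

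The ratio is 0.517 / 0.506 = 1.02, an increase of about 2%.

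**If the abstract's 60 were followed literally**

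60 × 0.80 = 48 completers (24 per arm), with a half-width of 1.96 × √(2/24) = 0.566. This applies only if the abstract overrides section 2.3.

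**What is not affected**

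The section's separate power calculation (d = 0.18, one-sided 5%, 80% power, 383 per group) reproduces: the noncentral t power at 383 per group is 0.8006.

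**The case against.** The strongest reply is that the discrepancy is trivial. The attrition rate is only approximate, 16.7% is not far from 20%, and the target of 60 was not derived from a power calculation. Section 2.3 rests it on prior imaging studies and feasibility, and calls the trial exploratory. Most of this stands, and it limits the severity. It does not rescue the sentence. The rate given is 20%, 72 is exactly 60 × 1.2, and the outcome is worded as a floor. Even at 16.7% the chance of reaching 60 is only 0.58.

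A second reply is that 60 in the closing power caveat of section 2.3 is not a contradiction. That is right: there it can be read as the completer target, which is the relevant number for a statement about power.

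Several stronger readings are tempting but are not supported:

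- *That the documents imply three different analysed sample sizes, or that the completer count sets the precision of every estimate.* Section 2.5.2.5 bases the primary analysis on all randomised participants, with mixed models and multiple imputation. The figures 57.6, 60 and 48 are completer counts. Dropout reduces information, but not simply by substituting the completer number.
- *That each arm must retain 30.* The 30 per group describes allocation. The stated expectation concerns the total only.
- *That the pilot will be judged a failure below 60 completers.* No retention or recruitment threshold is stated; 60 is an expectation.
- *That completion has no defined end, since annual visits are open-ended (section 2.1).* The main comparison is baseline to six months (section 3.3), so the six-month visit is the natural reading. Naming it is a clarification, not a further error.

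**Conclusion.** The point holds in two parts. First, the stated inputs of section 2.3 do not give its stated result: 72 enrolled at 20% attrition gives 57.6 expected completers, with about a 0.30 chance of 60 or more, and 60 is expected only at attrition of 16.7% or less. Second, the abstract's enrolment of 60 conflicts with the 72 in section 2.3, which itself gives both numbers without separating recruits from completers.

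Severity is minor to should-fix. The arithmetic slip costs 2.4 expected completers and about 2% in interval width, and no test, error rate or decision rule depends on it. The conclusion rests on taking attrition at the stated 20%. The probabilities further assume independent dropout at a common rate, and the half-widths use completers only.

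**What to change.** Wording only; no additional participants are needed.

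- **Section 2.3, enrolment sentence:** state that 72 will be randomised (36 per group), that about 57–58 are expected to complete the six-month assessment at 20% attrition, and that 60 is expected only if attrition is at most 16.7%.
- **Section 2.3, sentence on recruiting 60:** reword it as a target of 60 completers.
- **Abstract, Methods:** give 72 as the number enrolled.
- **Section 2.3, power caveat:** keep the evaluable number there, label it as completers and match it to the restated figure. Do not replace it with 72.

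The only cost is a slightly less favourable completer figure. Enrolling 75 (76 for equal arms) would also reconcile the text while keeping 60 expected completers, at the price of 3 to 4 more participants. So would stating attrition of at most 16.7%, if the sponsor's sources support it. Whichever is chosen, one enrolment number should appear throughout.
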